#### Statistical power

A meta-analysis of 31 studies evaluating interventions that target the intersection of body image and movement experiences among girls and women via randomised controlled trials reported a mean effect size of Cohen’s *d* = 0.18 on body image, which can be interpreted as a small-to-medium effect size. Based on conservative *d* = 0.2, an ICC of 0.02 within intervention delivery groups (as informed by a similar cluster trial of a body image intervention Craddock, Budhraja, Garbett, Nasution, Gentili, Rizkiah, Saraswati, Medise, White, Diedrichs & Williamson: Randomised Control Trial of Dove Confident Me Indonesia: Single Session. Forthcoming]), and an approximate distribution of 15 athletes per delivery group, a total sample size of 864 athletes (*N* = 432 per arm) would provide 90% power over a correlation between baseline and outcome data at T2 or about 0.6, considering alpha = 0.05. We will oversample to mitigate the effects of loss at post-intervention due to athletes’ absence or any other logistical difficulty. Therefore, the ideal sample size will be increased by 20%, leading to a minimum target of approximately 1,036 athletes (518 per randomised arm).

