#### Data analyses

Data preparation, assessment of baseline equivalence, hypothesis testing, and exploration will be undertaken using SPSS 28.0 (IBM Corp, 2021) and R Studio (R Core Team, 2021). Data will be screened to ensure scoring fidelity and data accuracy. Once the data validity checks are complete, scales’ scores will be calculated, score distributions will be assessed, and the data will be checked for outliers and any inaccurate influential observations. Missing data will be assessed across all outcomes and time points. Data will be analysed on an intention-to-treat basis and secondly using data from participants with at least 70% of the attention checks successful completed.

The primary analyses will be linear mixed models with random intercepts for all outcome measures (body esteem, body appreciation, self-objectification, attuned self-care, sports enjoyment, and affect). The models will include two main effects: study phase (i.e., repeated measures fixed effect factor with three levels: T2, T3, and T4), randomised arm (i.e., between-subjects fixed effect factor with two levels: intervention and control), as well as baseline levels of the outcome as a covariate. The model will also see two two-way interactions (i.e., randomised arm by study phase, randomised arm by baseline). Analyses will be run on an intention-to-treat basis, both with and without clusters including a random effect (i.e., intervention delivery group), in order to identify their potential significant impact [54].

For each outcome measure, a priori ANCOVAs will compare the two randomised arms at T2, controlling for baseline measures as covariates. These analyses will be repeated at T3 and T4. If the homogeneity of regression lines assumption is violated, the ANCOVA model will include a baseline by randomised arm interaction. Exploratory moderation and mediation analyses will be run to check whether any differences in intervention efficacy might be dependent on relevant demographic or baseline variables. To ensure valid statistical inferences, we will check for any potential assumption violation in all the models.

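### The trial is sized for clustering, but the clustered mixed model is not named as decisive and the T2–T4 ANCOVAs are written without a cluster term

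*Protocol article*

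**What the plan says.** The Abstract and the Participant recruitment and procedure section randomise organisations, and Randomisation and blinding places allocation at group level, 1:1. The Statistical power section takes "an ICC of 0.02 within intervention delivery groups" and "an approximate distribution of 15 athletes per delivery group", and concludes that "a total sample size of 864 athletes (*N* = 432 per arm) would provide 90% power".

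The Data analyses section calls linear mixed models the primary analyses. They cover T2, T3 and T4, with arm, phase, baseline and two interactions. On clustering it says: "Analyses will be run on an intention-to-treat basis, both with and without clusters including a random effect (i.e., intervention delivery group". The stated purpose is "in order to identify their potential significant impact". Neither version is given precedence.

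The next paragraph adds that "a priori ANCOVAs will compare the two randomised arms at T2, controlling for baseline measures as covariates", to be repeated at T3 and T4. The only further term it provides for is a baseline-by-arm interaction, if the regression slopes differ. It mentions no cluster effect and no cluster-robust standard error. The Abstract gives the primary outcome as the immediate change in body esteem, so the T2 comparison carries the most weight.

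**The concern.** Correlation within clusters follows from the way the trial allocates. It is a feature of the design that the analysis has to carry, whether or not it looks important in the data. The Statistical power section accepts this, because its sample size pays for clustering. The Data analyses section does not follow through. It plans two versions of each primary model with no rule for which one counts, and it sets out a T2 arm comparison as if girls had been randomised individually.

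An analysis that omits the cluster term gives standard errors that are too small and p-values that are too low. With two versions planned and neither designated, a favourable unclustered result could be reported as the finding. The Dissemination and Discussion sections make scale-up and public release depend on the programme proving effective, so a false positive would have consequences.

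**Working it through.** **Inputs (Statistical power section):** d = 0.2 with SD 1; ICC = 0.02; m = 15 per delivery group; baseline–T2 correlation r = 0.6; alpha 0.05; power 90%; 432 per arm. Sidedness is not stated. Two-sided is assumed because it reproduces the stated number.

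**1. Reproduce the plan's sample size.**
- Unadjusted: n per arm = 2 × ((1.960 + 1.282)/0.2)² = 525.4.
- Baseline adjustment: 1 − 0.6² = 0.64, so 525.4 × 0.64 = 336.2.
- Design effect: 1 + (15 − 1) × 0.02 = 1.28, so 336.2 × 1.28 = 430.4 per arm, or 862 in total. The plan states 432 and 864.
- Power at 432 per arm with this design effect: 90.1%.
- Without the design effect the answer would be about 336 per arm. With one-sided alpha it would be about 351. Neither matches, so the stated size presupposes a clustered analysis.

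**2. Error rate at one time point when clusters are ignored.**
- The standard error is too small by a factor of √1.28 = 1.13.
- Type I error = 2 × (1 − Φ(1.96/√1.28)) = 2 × (1 − Φ(1.732)) = 0.083.

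**3. Check by simulation.** Null trials with 29 clusters of 15 per arm (432/15 = 28.8), 20,000 runs, outcome ICC 0.02 and within-cluster correlation 0.6:

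| Cluster-level baseline–outcome correlation | ANCOVA, no cluster term | Cluster-level test, same data |
|---|---|---|
| 1.0 | 5.9% | 5.1% |
| 0.6 | 8.3% | 5.1% |
| 0 | 11.9% | 5.0% |

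**4. Range from the formula.**
- m = 15, ICC after baseline adjustment of 0.01, 0.03 and 0.05: 6.6%, 10.0% and 13.3%.
- ICC 0.02, m = 12, 20 and 30: 7.6%, 9.5% and 11.9%.
- If 15 is the recruited group size and losses bring 1,036 back to 864, then m = 15 × 864/1,036 ≈ 12.5. The design effect is 1 + 11.5 × 0.02 = 1.23 and the error is 7.7%.

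**5. Scope.** Steps 2 to 4 concern a comparison at a single time point: the ANCOVAs as written and, approximately, the T2 contrast from a mixed model without the cluster term. No error rate was derived for the three-phase unclustered model as a whole.

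**The case against.** The clustered mixed model is planned and will exist, and the article gives the label of primary analysis to the mixed models, not to the ANCOVAs. The mixed model's arm-by-phase terms also yield a T2 contrast. All of this stands, and it limits the point. A reader might infer that the trial's p-values in general carry an 8% error rate. The documents do not support that, because an analysis that respects the clusters holds about 5%.

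A reader might also infer that the cluster term will be dropped if it proves non-significant. The text does not say so. The stated purpose can equally mean comparing the treatment result with and without clustering, and the source cited there has not been seen. Nothing here relies on a pre-test of the cluster variance.

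The missing cluster term in the ANCOVAs is read from a condensed article, and a fuller plan may supply it. That part is therefore less certain than the explicit wording about running both versions. Even so, the ANCOVA paragraph does set out the model's terms and its one contingency, and the sentence on clusters belongs to the mixed-model paragraph.

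Finally, 8.3% is one value in a range. It assumes that the ICC of 0.02 remains after baseline adjustment. If cluster means at baseline predict those at T2 almost perfectly, the inflation nearly vanishes (5.9%).

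**Conclusion.** The point holds in a limited form. The plan sizes the trial for clustering but does not commit to a clustered result as the decisive one, and its separate T2–T4 ANCOVAs are written without any allowance for clusters. In those ANCOVAs, and in a T2 comparison from an unclustered model, the two-sided type I error is about 8% against a planned 5% at an ICC of 0.02 and 15 girls per group. Across plausible departures it is roughly 6–12%; an ICC of 0.05, well above the plan's assumption, would give 13.3%. The clustered mixed model is not affected in this way.

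One related matter affects the remedy. Organisations are randomised, whereas the random effect named is the delivery group. If an organisation contributes several delivery groups, a delivery-group effect alone may not capture the randomised unit. The article does not say how often this occurs, so no size is attached to it.

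**What to change.** In the Data analyses section:

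- Name the mixed model with a random intercept for the randomised cluster as the single primary analysis. The cluster is the organisation, with delivery group nested within it where an organisation has several. State that the term is kept whatever its estimate or p-value.
- Add the same term to the ANCOVAs at T2, T3 and T4.
- Keep an unclustered run only if it is labelled as sensitivity and not used for inference. It need not be deleted.
- A small-sample degrees-of-freedom correction is advisable with about 58 clusters, but it is secondary.

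The cost is one paragraph and slightly wider confidence intervals. No extra participants are needed at the planned ICC and group size, because the 864 already includes the design effect of 1.28. If several delivery groups per organisation are common and correlated with one another, that allowance should be rechecked.

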#### Ethical issues, approval, and trial registration

This research adheres to the ethical standards and guidelines put forth by the University of Minnesota and the University of the West of England. Specifically, participants will receive an overview of project aims, objectives, and research tasks prior to providing consent. Further, participation is voluntary, and participants may withdraw at any stage without justification or penalty. Irrespective of their completion stage, all participants will receive a debrief form that discloses the research aims, along with additional mental health resources (e.g., evidence-base websites, helpline contact details). Any serious adverse events will be reported to the universities’ ethics committees. This study was reviewed by and received approval from the ethics committees at the University of Minnesota (STUDY00012457) and the University of the West of England (HAS.21.03.120c). The study is registered with Clinical Trials.Gov (https://www.clinicaltrials.gov/ct2/show/NCT05594524).

#### Dissemination

In accordance with the broader aims of this research, which are grounded in CBPR principles, findings from this research will be widely disseminated beyond the academic setting (e.g., peer-reviewed publication and academic conferences). Research findings, as well as the intervention materials will be hosted on a freely accessible website, as well as promoted via promotional campaigns. If BCA proves effective, it will be scaled up and delivered to young people across the US and other English-speaking countries, with future plans including the translation and localisation of the programme for non-English speaking countries (e.g., France, India, Mexico).

## Discussion

This protocol reports on the co-creation, piloting, and planned cluster randomised controlled trial of a new intervention, Body Confident Athletes (BCA). This coach-led intervention aims to increase girls’ positive body image and sports enjoyment. An initial pilot assessed intervention feasibility, as well as the feasibility of conducting a two-armed cluster randomised controlled trial in the US. Findings from the pilot led to modifications to the intervention content (i.e., greater representation of girls with Disabilities in sport) and structure (i.e., reduced the core sessions from five to three), as well as modifications to the trial protocol (i.e., expanding the eligibility criteria and recruitment channels to include school athletic departments). Based on these amendments, the intervention and trials were deemed feasible with the main trial commencing 30 January 2023 (i.e., first wave of baseline assessments) and recruitment finishing 22 February 2023 (i.e., last opportunity to enrol). The main trial will assess the immediate (post-intervention) and short-term (1-month, 3-month) impact of BCA on girls’ body image (body esteem, body appreciation, attuned self-care, resisting objectification), sports enjoyment, and affect (positive and negative). At the completion of the trial, provided BCA is effective and does not require major revisions (e.g., is found ineffective or harmful), the intervention materials will be made freely available via an English website in October 2023.

This research makes several advancements in addressing the intersection of girls’ body image and sport experiences. To our knowledge, this is the first intervention on this topic to: 1) utilise a global and cross-national lens and community-based participatory research (CBPR) throughout the intervention development process; 2) target both risk and protective factors for body image and apply intervention techniques to sport-specific settings and scenarios; and 3) task shift intervention delivery to coaches. Relatedly, and to our knowledge, it is the first study on this topic to pilot test the feasibility of both the intervention and trial protocol prior to moving into a large-scale cluster randomised controlled trial. Collectively, these theoretical and methodological considerations allowed us to incrementally refine both the intervention (i.e., content, structure, and format) and the trial protocol (i.e., eligibility criteria and recruitment pathways). In turn, the main trial will be conducted on the most feasible intervention and under the most feasible conditions. If proven effective at enhancing girls’ positive body image and sports enjoyment in the US, BCA will be tested for effectiveness in other countries and cultures. Overall, these research efforts seek to increase BCA’s potential at improving girls’ positive body image and sports enjoyment across the world, which may possibly help with reducing genders disparities in sports participation.

## Data Availability

The intervention, Body Confident Athletes, will be freely available via a website that will be launched in October 2023. The datasets generated and/or analysed during the current study are not publicly available as per the data management and monitoring guidelines of the governing universities but are available from the corresponding author on reasonable request.

## Abbreviations

AE: Appearance Esteem
BCA: Body Confident Athletes
CBPR: Community-Based Participatory Research
CONSORT: Consolidated Standards of Reporting Trials of Electronic Health
HBI: Healthy Body Image
SPIRIT: Standard Protocol Items: Recommendations for Interventional Trials
T1, T2, T3, T4: Time One, Time Two, Time Three, Time Four
UK: United Kingdom
US: United States
WE: Weight Esteem
